### Baseline functional and clinical evaluation

Functional capacity and quality of life (QoL) are assessed by New York Heart Association (NYHA) classification [19], six-minute walk test (6MWT) [20], and Minnesota Living with Heart Failure Questionnaire (MLHFQ) using the official Danish version [21, 22].

### Echocardiography

Echocardiography is performed at baseline and 6-month follow up (6MFU) using a 3.5-MHz transducer and a commercially available system (Vivid E9, GE, Horten, Norway). Electrocardiogram (ECG)-triggered, two-dimensional (2D), tissue Doppler images (TDI), and color Doppler images are obtained during breath hold. A frame rate of 50–80 frames per second is intended. Echocardiographic images are stored in cine-loop format and analyzed offline (EchoPac BT201, GE, Horten, Norway). All measurements are averaged over three cycles. Simpson’s bi-plane method is applied to assess LV volumes and LVEF [23].

The latest mechanically activated myocardial segment is determined by speckle-tracking radial strain analysis in the LV short-axis view in the basal and mid-LV imaging plane. According to the standardized LV segmentation [24], the LV short axis (SAX) is divided into six myocardial segments. Time from QRS onset to peak radial strain is measured in the basal and mid-LV segments (Fig. 3a). LV mechanical dyssynchrony is determined as the time delay between peak radial strain in the mid-LV antero-septal and the posterior segment [17]. Where radial strain analysis is not applicable in the LV SAX view (TDI), time-to-peak longitudinal strain analysis performed in the mid-LV segments in the A4Ch, A2ch and long-axis views are applied to identify the latest activated myocardial segment [25]. Echocardiograms will be analyzed by two observers, and interobserver and intraobserver variability will be reported.

**Fig. 3 Fig3:**
[figure not shown]
Intervention group: electrical mapping. The local electrical activation delay is measured as time in milliseconds (ms) from QRS onset in the surface 12-lead electrocardiogram (ECG) to the maximum voltage change over time recorded in the local LV electrogram (EGM), reflecting the near-field activation of the myocardium according to the LV lead (QLV interval). The figure shows three examples of QLV measurements with the LV lead in a basal, mid, and apical position, exhibiting the longest QLV interval in the apical position. For simplicity, only the surface leads V2 and V6 and the local LV EGM (Pace 1–2) are shown

### Assessment of cardiac venous anatomy and LV lead position by cardiac CT

A contrast enhanced (Optiray 350 mg/ml, Covidien, Ireland) high-pitch spiral CT scan (Siemens SOMATOM Definition Flash or Siemens SOMATOM Force, Siemens, Forchheim, Germany) is performed for pre-implant assessment of cardiac venous anatomy. Sublingual nitroglycerin is administered prior to the scan. Data are acquired with 80–140 kV tube voltage. The scans are performed ECG-gated with full pulsing only in diastole (65–80% of the RR interval), and during breath-hold. The time-tracking technique is applied to determine contrast filling in the LV cavity (20 ml for the test bolus and 50 ml for the scan). Two successive high-pitch spiral scans are performed at 15 and 19 s after peak contrast filling of the LV cavity.

The scan with the best CS visualization is used for study purposes. Images are reconstructed iteratively (Siemens SOMATOM Force) or with filtered back-projection (Siemens SOMATOM Flash). Image analysis is performed in Syngo.via, using the InSpace application (Siemens, Forchheim, Germany) for evaluation of multi-planar and three-dimensional (3D) images, respectively (Fig. 3b and c). Contrast enhanced (40 ml) high-pitch ECG-gated CT using the same scan protocol is performed the day after implantation to determine final LV lead position. Cardiac CT will not be performed in the minority of patients with depressed renal function with estimated glomerular filtration rate (eGFR) < 35 ml/min/1.73 m2., thyrotoxicosis or in the case of former severe reactions to the contrast medium.

### Localization of the myocardial scar

Pre-implant ECG-gated Rb-PET is performed in all patients using a commercially available scanner (GE Healthcare, Buckinghamshire, UK). Briefly, intravenous injection of 1150 MBq rubidium is directly followed by a 7-min list mode scan of the heart. List mode data are subsequently re-binned into 27 dynamic frames (12 × 5, 6 × 10, 4 × 20, 4 × 40, and 1 × 60 s) and one static frame (2.5–7 min following initiation of the scan). Resting MP values are calculated from dynamic Rb PET/CT images and normalized for differences in rate pressure product (RPP) using an assumed population average value of 10,000 divided by the RPP. Data are analyzed using the commercially available automatic program Quantitative PET (Cedar-Sinai Medical Center, Los Angeles, CA, USA). Static data are displayed in polar map format and analyzed using the 17-segment model (Fig. 3d) [24]. Segments with a tracer uptake < 50% are considered as transmural scar tissue, those between 50 and 75% as non-transmural scar tissue, and those ≥ 75% are considered viable myocardium [26].

### Randomization and blinding procedures

After baseline clinical evaluation and pre-implant imaging, patients are allocated either to the intervention or the control group. Study data are recorded in a web-based case record form (CRF) with logging of all data entries. The CRF is also used for randomization using computerized permuted blocks of different sizes. Randomization is stratified according to ischemic or non-ischemic heart failure etiology. An external data manager is responsible for the CRF and has programmed a computerized random-number generator.

Patients and physicians responsible for enrollment, baseline and follow-up clinical evaluation, including imaging acquisition, are blinded to the allocated treatment. Information about randomization is available only to the physician performing the implant. Data related to the device implantation, post-implant device-tests, and optimization are collected and entered into the CRF by the physicians performing the implantation and the dedicated research nurses, to ensure blinding of the investigator collecting clinical and imaging data. Information on the randomization code will be available when all patients have completed the 6MFU and all statistical analyses have been performed.

### The applied strategies for cardiac resynchronization therapy

Intervention group: prior to implantation fluoroscopic venography is co-registered to the CT venography to ensure visualization of all available CS branches. During the implantation procedure, systematic electrical activation mapping of all available epicardial veins is performed using the LV electrode and/or a specialized mapping guidewire (Visionwire®, Biotronik, Berlin, Germany). Simultaneous local LV electrograms (EGM) and 12-lead surface ECGs are acquired (CardioLab IT, GE Healthcare). The local electrical activation delay is measured as the time interval from QRS onset in the surface ECG to the maximum voltage change over time recorded in the EGM, reflecting the near-field activation of the myocardium according to the LV lead (QLV interval) [12] (Fig. 4). The QLV interval is measured in the basal, mid and apical region of each CS branch. A quadripolar LV electrode will be used as first choice in all patients. The LV electrode is implanted at the site exhibiting the longest QLV interval (and thereby the latest local electrical activation) with acceptable pacing threshold and no diaphragmatic stimulation.

**Fig. 4 Fig4:**
[figure not shown]
SPIRIT figure of the ElectroCRT study protocol. ECG, electrocardiogram; NYHA, New York Heart Association; MLHFQ, Minnesota Living with Heart Failure Questionnaire; 6MWT, 6-minute walk test; Rb-PET MP, rubidium positron emission tomography myocardial perfusion imaging; CT, computed tomography; VV, interventricular; AV, atrioventricular; LV, left ventricular; LVEF, left ventricular ejection fraction; LVESV, left ventricular end-systolic volume, CRT, cardiac resynchronization therapy; 6MFU, 6-month follow up; QoL, quality of life; Nt Pro-BNP, N-terminal prohormone of brain natriuretic peptide, LVEDV, left ventricular end-diastolic volume

Immediately after the implantation, the VVd settings are programmed by the physician performing the implantation, to obtain the narrowest QRS width. This is performed by measuring QRS width as the maximal QRS duration in any lead in the 12-lead ECG recorded at five different VVd settings: (1) right ventricle (RV) stimulation 20 ms prior to LV stimulation, (2) simultaneous biventricular pacing, (3) LV stimulation 20 ms prior to RV stimulation, (4) LV stimulation 40 ms prior to RV stimulation, and (5) LV stimulation 60 ms prior to RV stimulation.

Control group: prior to implantation the fluoroscopic venography is co-registered to the CT venography to visualize available CS branches. After combining information from echocardiography, Rb-PET, and cardiac CT, the LV electrode is targeted towards the CS branch closest to the latest mechanically activated non-scarred myocardial segment. Basal and mid-LV segments of the CS tributaries are prioritized separately according to the relation with basal and mid-LV segmental mechanical activation delay. CT images of cardiac venous anatomy are available to the physician performing the implantation in a 2D short-axis view and in 3D volume-rendered reconstructions. The CS tributary closest to the optimal LV pacing site is labeled as first priority for LV lead placement. Tributaries closest to the second, third, or fourth latest activated segment with viable myocardium are chosen as the second, third, or fourth priority [17].

In the imaging group, the VVd is programmed to simultaneous biventricular stimulation. In both treatment groups, atrioventricular (AV) optimization is performed the day after implantation using the iterative method ensuring maximal separation of the E-wave and A-wave without termination of the A-wave [27].

### Endpoints

The primary endpoint is absolute change in left ventricular ejection fraction (LVEF) from baseline to 6MFU measured by 2D echocardiography. Secondary outcomes include relative percentage reduction in LV end-systolic volume (LVESV) and a combined clinical outcome measure of response to CRT at 6MFU defined as the patient being alive, not hospitalized for heart failure, and experiencing an improvement in NYHA functional class or/and > 10% increase in 6MWT [17]. Hospitalization for heart failure is defined as admission to hospital for more than 24 h with symptoms of congestive heart failure and need for intensified drug treatment for heart failure. Other secondary outcome measures include:All-cause mortality.Hospitalization for heart failure.Implantation procedure time.Procedural radiation exposure.Device-related complications.Indices of dyssynchrony and association between dyssynchrony, LV lead placement, and response to CRT.Changes in QoL, NYHA functional class, 6MWT, N-terminal prohormone of brain natriuretic peptide (Nt Pro-BNP), QRS duration, LV end-diastolic volume (LVEDV), LVESV, LVEF, mechanical dyssynchrony, and LV lead parameters (pacing threshold, sensing value, impedance).

### Sample size

We hypothesize that the intervention group strategy will result in an excess increase in LVEF of 4% compared with the strategy used in the control group, where an 8% increase in LVEF is expected [9]. To identify this absolute increase in LVEF of 12% in the intervention group and to achieve statistical power of 80%, the study will need a sample size of 98 patients, given a standard deviation (SD) of 7% in both groups, and a two-sided alpha value of 0.05. To achieve statistical power of 80% for the secondary endpoint of relative reduction in LVESV a sample size of 116 patients is needed, when assuming a 33% reduction in the control group and a 45% reduction in the intervention group (expected SD of 23% in both groups and given a two-sided alpha value of 0.05%). To achieve statistical power of > 80% with a margin of non-inferiority of 20% for the secondary endpoint of clinical response to CRT (assuming a 75% clinical response rate in the control group) we will need a sample size of 116 patients (given a two-sided alpha value of 0.05%). Taking into consideration expected loss to follow up in approximately 5% of patients, 122 patients are included.

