### Statistical analysis

All analyses will be conducted according to the intention-to-treat principle and will be performed before breaking the randomization code. Baseline characteristics are presented and compared clinically. Primary and secondary endpoints will be analyzed using linear regression for continuous variables and logistic regression for binary outcome measures, including heart failure etiology as a variable in the model. Multivariate regression analysis will be reported for absolute change in LVEF including baseline LVEF, heart failure etiology, sex, and baseline QRS width as covariates. Predictors of missing outcome values will be identified by comparing baseline characteristics and will be included in a multivariate regression model for sensitivity analysis. Intraclass correlation coefficients are computed to assess intraobserver and interobserver agreement for the echocardiographic parameters included in the primary endpoint: LVEF, LVEDV, LVESV assessed for 20 echocardiograms. A two-sided *P* value < 0.05 is considered significant.

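### Sample size section prints alpha as 0.05% for both secondary calculations: a stray percent sign for LVESV, while the non-inferiority sentence may need more than its removal

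*Protocol article*

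**What the plan says.** The Sample size section of the Protocol article contains three calculations in one paragraph.

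- **Primary, absolute change in LVEF:** "given a standard deviation (SD) of 7% in both groups, and a two-sided alpha value of 0.05", with no percent sign, giving 98 patients.
- **Secondary, relative reduction in LVESV:** 116 patients for 80% power, with mean reductions of 33% (control) and 45% (intervention) taken as the planning values. The bracket attached to this calculation reads "expected SD of 23% in both groups and given a two-sided alpha value of 0.05" and then has a percent sign.
- **Secondary, clinical response, non-inferiority:** control response 75%, margin 20%, power above 80%: "we will need a sample size of 116 patients (given a two-sided alpha value of 0.05", again followed by a percent sign. No response rate is given for the intervention arm.

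The paragraph ends by allowing for about 5% loss to follow-up and arriving at 122 patients. The Statistical analysis section gives one threshold for the trial: "A two-sided *P* value < 0.05 is considered significant". It sets no separate level for secondary endpoints.

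**The concern.** Read literally, 0.05% is 0.0005. For the two secondary calculations, the paragraph then states an alpha one hundredth of the one used for the primary endpoint and in the analysis section. An alpha, a power and a sample size have to fit together, and with the printed alpha these do not.

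The location matters more than it would for a slip in background text. The primary endpoint needs only 98 patients. The enrolled number rests on the 116 of the two secondary calculations (116 × 1.05 = 121.8, hence 122). The misprint therefore sits in the calculations that set the size of the trial, and a reader trying to reproduce them will fail.

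**Working it through.** **Inputs** (Sample size section, with 1:1 allocation from Study design): LVEF difference 12 − 8 = 4 points, SD 7; LVESV difference 45 − 33 = 12 points, SD 23; power 80%; non-inferiority margin 20 points, control response 75%.

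**Formula for two means**, per arm, normal approximation: n = 2 × (z for 1 − α/2 + z for power)² × (SD/difference)². The z value for 80% power is 0.8416.

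**Primary endpoint, as a check on method.** At two-sided 0.05: 2 × (1.9600 + 0.8416)² × (7/4)² = 2 × 7.849 × 3.0625 = 48.1, so 49 per arm and 98 in total. This is the plan's figure.

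**LVESV.** (23/12)² = 3.674.

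| Two-sided alpha | Calculation | Per arm | Total |
|---|---|---|---|
| 0.05 | 2 × (1.9600 + 0.8416)² × 3.674 = 57.7 | 58 | 116 |
| 0.0005 (as printed) | 2 × (3.4808 + 0.8416)² × 3.674 = 137.3 | 138 | 276 |

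The plan's 116 is reproduced exactly at 0.05. Power with 58 per arm is then 80.2% (79.6% by the exact t-test, which would ask for 118). One-sided 0.05 gives 92, so it does not explain the figure. Two-sided 0.05 is the level that fits.

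**Non-inferiority.** Per arm: n = (z for 1 − one-sided α + z for power)² × [p1(1 − p1) + p2(1 − p2)] / (margin + p2 − p1)², with p1 = 0.75 for control. The intervention rate p2 is not in the document, so two assumed values are shown.

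*Assumed p2 = 0.75.* The variance factor is 0.375/0.04 = 9.375.
- One-sided 0.05: (1.6449 + 0.8416)² × 9.375 = 58.0, so 58 per arm and 116 in total (power 80.0%).
- Two-sided 0.05, that is one-sided 0.025: 7.849 × 9.375 = 73.6, so 74 per arm and 148 in total. Power with 58 per arm: 0.20/√(0.375/58) − 1.960 = 2.487 − 1.960 = 0.527, which is about 70%.

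*Assumed p2 = 0.80.* The variance factor is (0.1875 + 0.16)/0.25² = 5.56.
- Two-sided 0.05: 7.849 × 5.56 = 43.6, so 44 per arm and 88 in total for 80% power. For 90% power the total is 118, so 116 patients give just under 90%.

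Under equal rates, deleting the percent sign leaves a sentence that still does not give 116. Under an 80% intervention rate, 116 patients at two-sided 0.05 do give power above 80%. The document does not say which was assumed.

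**The case against.** The strongest reply is that this is a notational slip which the document resolves itself. The primary calculation uses 0.05, the Statistical analysis section fixes a single rule of two-sided P below 0.05, and the LVESV inputs return 116 at that level. Once the percent sign is removed, the LVESV sample size, test and threshold are all unchanged. Enrolment has also closed. All of this stands, and it is why the point is minor. It does not make the printed alpha correct.

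Two stronger readings are tempting, and the document supports neither.

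- A reader might infer that the trial is badly underpowered for LVESV, because 116 patients tested at 0.0005 would have power of only about 23% by the t-test (25% by the normal approximation). No test at 0.0005 is planned anywhere. The figure shows only that the printed level cannot be the one used.
- A reader might infer that the secondary endpoints have a deliberately strict, multiplicity-protected level, since the sign appears in both secondary calculations and not in the primary one. The document mentions no such adjustment and gives the secondary endpoints no level of their own. Nor does a stray percent sign justify asking for a multiplicity statement; that commonly belongs in an analysis plan, which is not shown.

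It is also fair to object that the hundredfold discrepancy describes LVESV only. For non-inferiority, the level that gives 116 depends on an intervention rate the document does not state.

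**Conclusion.** The printed alpha of 0.05% is wrong in the LVESV sentence. It contradicts the rest of the document and cannot produce the stated 116 patients, which follow from two-sided 0.05. This conclusion needs no assumption beyond the plan's own inputs. The LVESV sample size stands.

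The same percent sign in the non-inferiority sentence conflicts with the analysis section in the same way, but what the correct statement should be is open. It depends on the assumed intervention response: 148 patients are needed at two-sided 0.05 with 75% in both arms, and 88 with 80% in the intervention arm. Whether the claimed power above 80% holds therefore cannot be settled from the document.

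Severity is minor. Neither the primary calculation of 98 patients nor its threshold is affected.

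**What to change.** In the LVESV sentence, give alpha as two-sided 0.05 (5%). Nothing else in that sentence needs to change.

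In the non-inferiority sentence, remove the percent sign and state four things together: the alpha, whether it is one-sided or two-sided, the response rate assumed in the intervention arm, and the power that 116 patients then give. If the calculation used one-sided 0.05 with equal rates, say so. If two-sided 0.05 was intended with equal rates, report power of about 70% in place of the claim of more than 80%.

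The cost is a correction to two sentences, and the sponsor needs only to look up the inputs of the original non-inferiority calculation. No change to enrolment or to the planned LVESV analysis follows.

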## Methods

### Study design

The Electrically versus Imaging-guided Implant of the Left Ventricular Lead in Cardiac Resynchronization Therapy Study (ElectroCRT) is a prospective, patient-blinded and assessor-blinded, single-center, randomized, controlled trial. Study participants are allocated 1:1 to either the intervention group or the control group as follows:Intervention group (electrically guided) including pre-implant cardiac computed tomography (CT) to visualize cardiac venous anatomy, procedural electrical activation mapping of all available coronary sinus (CS) branches, placement of the LV lead to pace the site of latest electrical activation, and procedural VVd optimization to achieve the shortest possible QRS duration.Control group (imaging-guided) including pre-implant cardiac CT to visualize cardiac venous anatomy, speckle-tracking echocardiography to identify the LV myocardial segment with the latest mechanical activation, and myocardial perfusion (MP) imaging (^82^Rubidium positron emission tomography (Rb-PET)) to localize the LV myocardial scar. The LV lead is targeted towards the CS branch closest to the latest mechanically activated non-scarred segment and simultaneous biventricular stimulation is applied [17].

One day prior to implantation, all patients undergo identical pre-implant clinical evaluation and imaging acquisition after providing written informed consent. Patients are followed for 6 months. The study course is illustrated in Figs. 1 and 2.

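### If both arms truly respond at 75%, 116 patients give about 70% power for non-inferiority of clinical response at two-sided 0.05, not the stated figure above 80%

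*Protocol article*

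**What the plan says.** The Sample size section of the protocol article gives three calculations. The first is for the primary endpoint, change in LVEF: 98 patients, "given a standard deviation (SD) of 7% in both groups, and a two-sided alpha value of 0.05". The second is for relative reduction in LVESV: 116 patients. The third is introduced by "To achieve statistical power of > 80% with a margin of non-inferiority of 20% for the secondary endpoint of clinical response to CRT", is based on "assuming a 75% clinical response rate in the control group", and concludes that "we will need a sample size of 116 patients (given a two-sided alpha value of 0.05". In the second and third calculations the alpha is followed by a percent sign.

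The third calculation names no response rate for the intervention group. The section then closes with "Taking into consideration expected loss to follow up in approximately 5% of patients, 122 patients are included".

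The Study design section says "Study participants are allocated 1:1 to either the intervention group or the control group". The Statistical analysis section applies one rule to all endpoints, a two-sided P "value < 0.05 is considered significant". It analyses binary outcomes by logistic regression with heart failure etiology in the model. The article mentions neither a one-sided 5% test nor a 90% confidence interval.

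**The concern.** A non-inferiority test at a two-sided level of 0.05 compares the lower limit of the 95% confidence interval with the margin, which is a one-sided test at 0.025. With a 75% response in each arm and a 20-point margin, 116 patients looked too few for 80% power at that level and about right for a one-sided test at 0.05. The printed power would then belong to a different test from the one printed beside it.

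At stake is how a reader judges the non-inferiority result. The article gives this endpoint its own power claim. If the real chance of confirming true non-inferiority is about 70%, the risk of an inconclusive result is about 30%, where the text implies less than 20%. An inconclusive result would then be weaker evidence of a real deficit than the reader is led to think.

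**Working it through.** **Inputs**
- Control response 75%, margin 20 percentage points, power above 80%, N = 116, enrolment 122 with about 5% loss: Sample size section.
- Allocation 1:1, so 58 per arm at 116 and 61 per arm at 122: Study design section.
- Intervention response rate: not stated. Assumed 75% (true difference zero); a range is shown in step 4.
- Alpha: read as 0.05, for the reasons in step 1.

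**Step 1. What the percent sign means.** The LVESV calculation carries the same percent sign. With a difference of 12 points (45% against 33%) and an SD of 23, n per arm = 2 × (1.960 + 0.842)² × 23² / 12² = 57.7, so 58 per arm and 116 in total, which is the printed figure. At a literal two-sided 0.0005 it would need 276. The primary calculation, printed with 0.05, gives 2 × (1.960 + 0.842)² × 7² / 4² = 48.1, so 49 per arm and 98 in total, again as printed. Alpha is therefore 0.05. Taken literally, the non-inferiority calculation would have about 16% power at 116 and would need 352 patients.

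**Step 2. Reproducing 116.** For non-inferiority with equal true rates (unpooled normal approximation):

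n per arm = (z_alpha + z_0.80)² × 2 × 0.75 × 0.25 / 0.20² = (z_alpha + 0.842)² × 9.375

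- One-sided 0.05 (z = 1.645): 57.96, so 58 per arm, **116** in total.
- Two-sided 0.05, that is one-sided 0.025 (z = 1.960): 73.58, so 74 per arm, **148** in total (about 156 enrolled with 5% loss).

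**Step 3. Power at the planned size.** Power = Φ(0.20 / SE − z_alpha), with SE = √(0.375 / n per arm).

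- 58 per arm: SE = 0.0804 and 0.20 / SE = 2.487. With z = 1.645 the argument is 0.842 and power is 80.0%. With z = 1.960 it is 0.527 and power is **70.1%**.
- 61 per arm (all 122 evaluable): SE = 0.0784 and 0.20 / SE = 2.551. With z = 1.960 the argument is 0.591 and power is **72.3%**.

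The gap does not come from the approximation. Exact enumeration of the Wald-interval test at 58 per arm gives 70.1% with the 95% interval and 80.5% with the 90% interval. The Farrington-Manning method gives 69.8% at two-sided 0.05 and 74.0 patients per arm for 80% power. A continuity correction raises the requirement to 168 in total.

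**Step 4. Dependence on the missing intervention rate.** With 116 patients, two-sided 0.05 and 75% in the control arm, power = Φ((0.20 + p − 0.75) / SE − 1.960), where SE = √((0.1875 + p(1 − p)) / 58):

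| Intervention rate p | Power |
|---|---|
| 72% | 54.6% |
| 75% | 70.1% |
| 76% | 74.9% |
| 77% | 79.2% |
| 78% | 83.2% |
| 80% | 89.8% |

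Power reaches 80% at an intervention rate of about 77.2%.

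**The case against.** The strongest reply is that the article never says the two rates are equal. Its Background section hypothesizes that the electrically guided strategy does better, and the LVEF and LVESV calculations both assume a benefit. An unstated advantage of two to three points would bring power at 116 to about 80% at two-sided 0.05. LVESV already requires 116, so the sentence may simply report power checked at that size. This stands as a limit on certainty. A reader might infer that 116 can come only from a one-sided test; the document does not support that. A one-sided 5% test with equal rates is the likeliest explanation, because it gives both 116 and a power just above 80%, but it is not the only one. The reply does not rescue the sentence, which gives only one rate.

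A reader might also infer that non-inferiority will be declared from a 90% interval, doubling the one-sided error from 2.5% to 5%. Nothing in the article says so; its stated rule is a two-sided P below 0.05. That risk arises only if the sponsor does intend such an interval.

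A third inference would be that the trial is too small. The primary figure (98) and the LVESV figure (116) both reproduce at two-sided 0.05, and 116 × 1.05 = 121.8 gives the enrolment of 122 from LVESV alone.

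Finally, the 70% refers to an unadjusted risk difference, whereas the planned analysis is a logistic model with etiology. That is fair: the figure is approximate for that model.

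**Conclusion.** The point holds in a conditional form. With true response rates of 75% in both arms and alpha read as 0.05, the printed sample size and power do not go with the printed two-sided level. Power is about 70% with 116 evaluable patients and 72% with 122, against a claim above 80%; 80% would need 148. The equal-rates assumption is conventional but is not stated, and over intervention rates from 72% to 78% power runs from 55% to 83%.

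Severity is moderate. The error overstates the power of a secondary endpoint. It does not touch the primary endpoint or the enrolment target, and it does not establish an inflated type I error.

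**What to change.** In the Sample size section:
- state the intervention response rate assumed for the non-inferiority calculation;
- print alpha as 0.05, without the percent sign, here and in the LVESV calculation;
- if that rate is 75%, replace the claim of more than 80% power with about 70% at 116 evaluable patients, using the lower limit of the two-sided 95% interval, which matches the significance rule in the Statistical analysis section; if another rate was assumed, give the power that follows from it;
- say that the power is for an unadjusted risk difference and is approximate for the planned logistic model.

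If the sponsor intended a one-sided 5% test (90% interval), the text should declare that in place of the two-sided wording; 116 patients and 80% power are then consistent at equal rates.

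The cost is wording only, with no added patients. The downside is that, at equal rates and two-sided 0.05, a published secondary power becomes less favourable.
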